#### Attrition and sensitivity analysis

We expect an attrition rate of approximately 20%. Attrition may be greater for some clinical groups than for others (e.g., spousal caregivers of a PWD. If that is the case, variables of interest may be associated with attrition, and missing data will not be at random. This possibility could then bias results. To address this possibility, we will test to determine whether missing data are missing at random, by investigating if baseline measures may predict attrition and employ a statistical test to determine missingness [46–48]. If missing at random is observed, then the planned analysis will be stratified accordingly.

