##### Sample size calculation

Sample size was based upon the proposed longitudinal analysis investigating the effect of clinical group and relationship characteristics on changes in the primary outcomes over time. With an initial sample size of 300 couples (600 individual participants) and a potential dropout rate of 20% per group, we have powered the analysis to provide useful outcomes with a sample size of 240 dyads [41]. We have calculated the necessary sample size to sufficiently power the analyses for the smallest clinically substantive effect on the outcomes using the Geriatric Depression Scale scores in each of our three groups (cognitively normal controls, MCI, and AD). We made the following assumptions: 1) the minimum detectable effect size is 0.20, 2) there is 1 baseline measurement and either 3 or 5 post-baseline measurements, 3) two-tailed alpha error is 0.05, 4) power was set 0.8, and 5) the within-person association for over-time measurement is 0.7. With these assumptions, the study will need 50 patients for 3 follow-up measurements and 48 patients for 5 follow-up measurements per clinical group to adequately investigate the primary outcome, Geriatric Depression Scale scores [42]. The addition of covariates as well as multiple predictor variables and attrition will necessarily reduce this power; therefore, we have increased the sample size for those groups that may suffer most from attrition and offer the most clinical relevance (MCI and AD). Also, we will use model-building techniques (e.g., backward elimination) to fit the most parsimonious models. The use of sensitive and reliable measures and employing mixed-effects models to analyze repeated measures, which preserve all available data, will also, in general, improve power [43]. Lastly, the use of continuous predictor variables when available, e.g., MoCA score should also increase power over the use of categorical variables. With a sample of 300 couples at baseline, we are well powered to conduct the proposed analyses.

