Aim 2: To evaluate the change in the couple’s relationship, the potential causative factors that contribute to change in relationship characteristics, and the implications this change holds for the wellbeing of each member of the couple. Parameterization of repeated measures models [44]. The same fundamental procedures will be used for fitting all repeated measures models in this proposal. Because respondents will not be randomized, there may be differences across groups at baseline (e.g., age, education, relationship style). Therefore, we will include baseline measures in the trajectory analysis. Time will be treated as linear, but quadratic terms may be included if such a trend is graphically suggested. Correlation structures will be fit as autoregressive, generally the most appropriate for repeated measures data. Distributions of dependent variables will be either normal with an identity link or binary with a logit link. Models will be fit in SAS PROC GENMOD or PROC MIXED. For this aim, models will include a group by time interaction and will adjust for baseline variables. The model will be reduced in a backwards elimination fashion, removing variables that are non-significant and not important confounders. A significant interaction term in the final model will imply a significant difference in trajectories between groups, in which case adjusted mean and rates of changes will be presented separately for each time point. Post hoc analyses may involve testing pairwise comparisons across disease severity at specific time points or testing hypotheses around specific types of trajectories based upon observation of the adjusted least-square means or predicted probabilities by severity and time. Any post hoc analyses would be considered exploratory and p-values would be adjusted for multiple comparisons.

Longitudinal data will allow us to determine what relationship variables remain relatively static or are dynamic throughout the study and disease progression. This information will provide insight into what relationship characteristics may be responsive to psychosocial interventions. In addition, observing changes over time, via time-varying predictors and outcomes, will provide a closer approximation of causal inference; baseline severity along with changes in the relationship may be predictive of outcomes.

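### The attrition rule tests for missing at random with a check that cannot show it, and triggers stratification on the result opposite to its own concern

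*Protocol article*

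**What the plan says.** All references are to the protocol article.

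- **Attrition and sensitivity analysis.** Attrition of about 20% is expected, possibly higher in some clinical groups. In that event, the section says, "variables of interest may be associated with attrition, and missing data will not be at random". The planned response is: "we will test to determine whether missing data are missing at random, by investigating if baseline measures may predict attrition", together with a statistical test that is cited but not named. The action is: "If missing at random is observed, then the planned analysis will be stratified accordingly". No action is given for the opposite result.
- **Statistical analysis plan, Aim 2.** The test of interest is the group-by-time interaction. Outcomes are normal with an identity link or binary with a logit link. "Correlation structures will be fit as autoregressive, generally the most appropriate for repeated measures data". "Models will be fit in SAS PROC GENMOD or PROC MIXED". Models are reduced by backward elimination.
- **Sample size calculation.** The section counts on "employing mixed-effects models to analyze repeated measures, which preserve all available data".
- **Overview and Assessment (Process).** Impaired participants leave the study at a MoCA score of 12 or less or on loss of capacity. Data from the assessment at which capacity is judged lost are excluded. The partner continues.

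**The concern.** The section uses the missing-data terms in a way that makes its rule unworkable. It treats any association between attrition and the study variables as proof that data are not missing at random, although dependence on observed variables alone is what MAR means. It proposes to test a condition that observed data cannot confirm. It then attaches the remedy to the reassuring result and leaves the worrying one without a response.

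The group-by-time comparison in Aim 2 is at stake. The groups differ in expected attrition, and the impaired groups lose participants because of the decline under study. An analyst who follows the rule could declare the data missing at random, stratify, and report the trajectories as protected against dropout when they are not.

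**Working it through.** **1. The plan's own figure.** The sample-size section assumes "a potential dropout rate of 20% per group, we have powered the analysis to provide useful outcomes with a sample size of 240 dyads". 300 × (1 − 0.20) = 240, which agrees with the 20% in the attrition section. The point does not rest on this figure.

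**2. What the check can show.** Let R be the dropout pattern, X the baseline measures, and Y_obs and Y_mis the observed and missing outcomes.

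- MCAR: P(R | X, Y_obs, Y_mis) = P(R)
- MAR: P(R | X, Y_obs, Y_mis) = P(R | X, Y_obs)
- MNAR: P(R | …) still depends on Y_mis

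The check relates R to X.

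| Result | Ruled out | Still open |
|---|---|---|
| X predicts attrition | MCAR | MAR, MNAR |
| X does not predict attrition | nothing | MCAR, MAR through follow-up scores, MNAR |

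Neither row establishes MAR. The difference between MAR and MNAR lies in Y_mis, so an unnamed further test on observed data cannot settle it without untestable assumptions.

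**3. What the rule then does.**

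- *On the section's own usage* (association means not at random), finding predictors leads to no action. Finding none leads to stratification, with no predictor to stratify by.
- *On the standard usage*, MAR is the case in which a correctly specified likelihood model needs no stratification.
- *If the trigger is a slip for not at random*, the check still cannot establish MNAR, and stratifying on an observed variable does not remove dependence on unobserved values.

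**4. Missingness that the check does not see.** Withdrawal at a MoCA threshold or on loss of capacity depends on follow-up status. Baseline measures are at best a proxy for it.

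**5. Whether the planned models protect against MAR dropout.** The inputs from the article are 7 visits (baseline, then every 6 months for 3 years), within-person correlation 0.7 and AR correlation. The true effects and the dropout models are assumptions.

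*One group, true change 0.40 SD, true correlation exchangeable, logit(dropout) = constant + 1.2 × previous score:*

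| Cumulative dropout | AR(1) working matrix (GEE) | Maximum-likelihood AR(1) |
|---|---|---|
| 12% | 0.353 | 0.352 |
| 20% | 0.32 | 0.32 |
| 27% | 0.301 | 0.295 |
| 41% | 0.240 | 0.230 |

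Likelihood with the true covariance gave 0.40 at 20% dropout. The shortfall of AR(1) there is (0.40 − 0.32)/0.40 = 20% from rounded values, about 19% unrounded. With true AR(1) correlation both AR(1) fits gave about 0.40.

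*Two groups, true group-by-time slope 0.20 SD per year, normal outcome:*

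| Dropout mechanism | True correlation | AR working matrix | True covariance |
|---|---|---|---|
| Previous score, impaired group only (about 18% overall) | exchangeable | 0.167 | 0.199 |
| Previous score, impaired group only (about 18% overall) | AR(1) | 0.200 | 0.200 |
| Previous score, both groups (about 19%) | exchangeable | 0.189 | 0.200 |
| Covariates in the model only (about 23%) | either | 0.199–0.200 | 0.199–0.201 |

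The bias is (0.200 − 0.167)/0.200 ≈ 17% in the first row and (0.200 − 0.189)/0.200 ≈ 5% in the third.

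*Binary outcome, AR-working GEE, dropout driven by the previous score in the impaired group:* 0.242 against 0.334 with complete data (1 − 0.242/0.334 ≈ 27% too small) under exchangeable correlation, and 0.293 against 0.326 (about 10%) under AR(1). With covariate-driven dropout, observed and complete data agreed within about 0.001.

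**The case against.** The most charitable reading is that the trigger is a slip and that the authors mean to stratify by whichever baseline measures predict dropout. That amounts to conditioning on observed predictors. It is helpful under MAR and costs some precision. This reading is fair, but it still does not address MNAR, the problem the section names, and the test still cannot show which state holds.

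A reader might infer several stronger claims that the article does not support.

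- *GEE always needs MCAR.* It does not. Dropout that depends only on covariates in the model caused no material bias above, and differential attrition by clinical group, the section's own example, can be of that kind. The article never names GEE; it is inferred from PROC GENMOD with a correlation structure.
- *PROC MIXED would be unbiased where GENMOD is not.* For normal outcomes this fails. With AR(1) imposed, likelihood was as biased as GEE, so the cause is the wrong covariance.
- *The sample-size section and Aim 2 contradict each other.* They can be read together as MIXED for normal outcomes, including the Geriatric Depression Scale score, and GENMOD for binary ones.
- *Stratification means by dropout status, conditioning on a post-baseline event.* The preceding sentence concerns baseline measures, so this reading is unlikely and no size should be attached to it.

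The absence of an MNAR analysis from a journal article is not itself an error, since a fuller document may hold one. The rule that the article does state remains wrong.

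**Conclusion.** The point holds. The check bears only on MCAR, the trigger runs against the section's own reasoning, and stratification would not correct MNAR dropout. These conclusions follow from the text and need no simulation. Follow-up withdrawal linked to decline makes them relevant to this study.

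The modelling part is conditional. If dropout depends on earlier outcomes and the true correlation is not AR(1), the planned AR(1) structure biases the slope by either fitting method: about 19% in the single-group scenario at 20% dropout, and about 5% to 17% for the group-by-time slope at about 18–19% dropout. If AR(1) is true, or dropout depends only on covariates kept in the model, the bias for normal outcomes is nil or negligible. For binary outcomes fitted by GEE, bias of about 10% remained in the impaired-group scenario even when the underlying correlation was AR(1). The dropout coefficients and true effects are assumptions, so these figures show possible size and are not forecasts.

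**What to change.** 1. Delete the test for MAR and the stratification rule.
2. Report baseline and follow-up predictors of attrition descriptively, by clinical group. Keep them in the models, exempt from backward elimination.
3. For normal outcomes, use likelihood mixed models with a covariance not fixed as autoregressive: unstructured, or random effects plus AR.
4. For binary outcomes, use a likelihood mixed model (for example PROC GLIMMIX with quadrature) or inverse-probability-weighted GEE.
5. In place of the stratification rule, specify one MNAR sensitivity analysis by clinical group, for example a delta shift, using the reasons recorded on the Status Change Form.

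The cost is a rewrite of the attrition section and one sentence under Aim 2, modest programming, and a few more covariance parameters to estimate. No new data are needed, and the withdrawal rules stay as they are.

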## Discussion

The burden of ADRD on older couples is especially poignant, as they generally weather the illness together, with shrinking social networks to support them. Relationship characteristics have been shown to impact dementia outcomes for both the caregiver and the PWD. However, there are many limitations to prior research on relationship characteristics and dementia outcomes, including an almost exclusive focus on cross-sectional data collection, small sample sizes, and unexamined potential confounds that limit the interpretation of the importance of relationship factors. Longitudinal study of dyads living with ADRD is essential to understanding how relationship characteristics change over time and contribute to health outcomes for caregivers and persons with dementia. While relationship quality has an impact on both the caregiver and the care-recipient; the relationship between them from both their perspectives has rarely been studied.

The person who takes on the caregiving role may or may not consider him or herself a caregiver. This study will illuminate our understanding of when and why people identify themselves as caregivers or choose not to. Variability in interpretation of the caregiving role may be accounted for by the impact of other characteristics of each of the members of the dyad that are being investigated in this study.

Understanding the effects of dementia on couple relationships is a critical step needed to optimize existing evidence-based approaches and develop new ones for maintaining the wellbeing of caregivers and PWD. The findings of this study will inform the development of interventions to maximize the wellbeing of both members of a couple as one of them experiences cognitive decline and dementia.

## Data Availability

The investigator who proposed to use the data will have access to the data upon reasonable request. Requests should be directed to [contact]. To gain access, data requestors will need to sign a data access agreement.

## Abbreviations

ADRD: Alzheimer’s Disease and Related Dementia
MCI: Mild Cognitive Impairment
PWD: Person with Dementia
